
### Data analysis plan

Data will be entered by trained MDA delivery teams under the supervision of highly trained and experienced local supervisors. Senior trial management will regularly review data entry and offer retraining as needed. Sample ID numbers will be electronically captured or double entered. A communication network will be established with remote villages to facilitate monitoring and correction of errors found on review.

All analysis will be intention-to-treat. Analysis will be performed using STATA software (StataCorp) and R.

Cluster-level, arm-level and overall demographic characteristics will be presented using descriptive statistics, including age, sex, bed net use, household size and village/cluster populations.

#### Primary outcome

Trial arms will be compared using a t-test on cluster-level malaria qPCR prevalences. A risk difference, 95% CI and p value will be presented. Analyses adjusting for age groups (<5 years, 5–14 years, 15 years and above), bed net use and the presence of a health centre will be presented for this and all secondary outcomes.

#### Secondary outcomes

As for the primary outcome, using data from the year 1 survey.Cluster-level incidence rates will be compared using a t-test. If the distribution is markedly skewed, then the natural logarithm of each cluster-level summary will be taken. If some clusters have zero events, then 0.5 events will be added to each cluster. Rate differences, 95% CI and p value will be presented.As for outcome 2, using RDT-confirmed incidence rates from the two annual cohorts of children.As for outcome 3, using qPCR-confirmed incidence rates. Serological analysis described in outcome 5.Cluster-level serological responses to malaria antigens will be presented as both continuous median fluorescent intensity (MFI) data, a proxy for antibody titres, and binary seropositivity prevalence, with a seropositivity threshold of three standard deviations above the mean malaria-naïve MFI responses. MFI will be compared between arms using mixed effect linear regression, with a random effect for cluster. Seropositivity will be compared in the same way as the primary outcome, including analysis by age group. Cluster-level antigen-specific seroconversion rates (SCR) will be generated using serocatalytic models relying on seroprevalence, and age-seroprevalence plots will be generated by fitting data to a reversible catalytic conversion model using maximum likelihood methods. Trial arms’ SCR will be compared using a t-test.^53^As for outcome 5, using the gSG6 antigen and not employing SCR.Cluster-level anopheline parity will be compared between arms using a t-test. Adjustment will be made for species, MDA round, time relative to MDA date, temperature, humidity and rainfall. Parity difference, 95% CI and p value will be presented.The proportion of each species identified, and mosquito densities, will be presented by cluster and arm, and compared using χ^2^ and t-tests. Adjustment will be made for study month and year. Differences, 95% CIs and p values will be presented. If the distribution of densities is markedly skewed, a log transformation will be applied. SR will be compared between arms using a t-test on cluster-level SR with adjustments and covariates as described for parity analysis above. Risk difference, 95% CI and p value will be presented. EIR will be compared with a t-test on cluster level summaries.Species composition and level of resistance will be presented using descriptive statistics. Dose–response curves will be generated for each insecticide and probit regression analysis will be performed on these data using maximum likelihood or least squares methods.The number of alleles associated with antimalarial resistance will be compared over time, before and after MDA. However, appropriate statistical tests will need to be selected depending on the allele sample size before and after MDA.Descriptive statistics will be presented on the number, nature, severity and relatedness of all reported AE, with additional details for serious AE. Cluster-level and age-group data will be presented. Rates will be compared between arms.As for the primary outcome and outcome 5.Cluster-level, arm-level and overall coverage will be presented for each month and year of intervention, and for the trial overall. The denominator for these proportions will be the total number of people recorded on MDA administration records by distributors in each cluster, whether receiving MDA or not. Refusals, exclusions and absences will be presented similarly.Qualitative and quantitative analysis of MDA acceptability, feasibility and access will be outlined in a separate protocol.Cost-effectiveness analysis will be detailed in a separate protocol.

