#### Secondary outcomes

Population-based prevalence of *P. falciparum* parasitaemia in all ages, detected by qPCR, during the peak transmission season after the first year of MDA.Incidence of clinical malaria confirmed by *Plasmodium spp.* lactate dehydrogenase/histidine-rich protein 2 (pLDH/HRP2) rapid diagnostic test (RDT), determined through passive surveillance of all malaria cases presenting to health facilities throughout the trial.Incidence of clinical malaria identified by RDT (CareStart Malaria PAN pLDH) during active surveillance of a cohort of children aged 5–14 years, during the intervention and peak transmission season.Incidence of malaria infection identified by qPCR and serological analysis during the same period in this cohort of children.Age-adjusted prevalence of serological markers indicating recent exposure to *P. falciparum*.Prevalence of serological markers of recent *Anopheles* exposure.Parity, as a measure of *An. gambiae* sensu latu survival, measured in mosquitoes caught using indoor CDC light traps 7–14 days after the final MDA round in year 1 and year 2.Mosquito species composition, population density and SR in mosquitoes caught using indoor CDC light traps.Prevalence of resistance to pyrethroids in anopheline mosquitoes using bioassay methodologies.Prevalence of resistance to artemisinin and partner drugs in humans using molecular markers of resistance.Safety of intervention through monitoring of AE.Impact on IVM-susceptible NTDs (scabies, strongyloidiasis, other STHs and LF), headlice and bedbug infestation using clinical and serological parameters.Cluster-level intervention coverage estimates.MDA acceptability, feasibility and access.Cost effectiveness of adjunctive IVM in this setting.

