#### Secondary

A survey, identical to the primary outcome survey, will be conducted after 1 year of MDA.On the last day of every month, data on RDT-confirmed incident malaria cases will be recorded from each of the 10 health centres on included islands: age, sex, cluster, fever, RDT performed, RDT result and treatment provided.Cohorts of 50 children aged 5–14 years will be followed in 18 clusters. Households will be randomly selected from household-head lists of yolk villages. One child will be randomly selected to participate from each household, more if there are fewer than 50 eligible households. A new cohort will be selected in year 2. Participants will be visited 7–14 days after each round of MDA, as well as during the peak transmission surveys for a total of 8 timepoints. Age, sex, village, GPS and temperature will be recorded. Febrile children will be offered an RDT and treated if positive. All children will be asked about intercurrent clinical malaria episodes, trial adherence and bed net usage. A DBS will be taken for molecular and serological analysis.Assessed as for outcomes 3 and 5.Serological analysis will be performed on DBS taken during the cross-sectional and cohort surveys described above using a multiplex bead assay on the Luminex MAGPIX platform. The included antigens have antibodies, which are associated with recent or long-term exposure to, and/or protection from, *P. falciparum*: MSP1.19, AMA1, GLURP.R2, EBA175.RIII.V, EBA181.RIII.V, Etramp5.Ag1, Etramp4.Ag2, HSP40.Ag1, CSP, SBP1, Hyp2, GEXP18, Rh2.2030, Rh4.1 and Rh5.2.^51–53^Assessed as for outcome 5.One yolk village will be randomly selected per cluster. Households will be randomly selected in these villages using household-head lists (10 households/cluster in year 1; 15/cluster in year 2). A CDC light trap will be placed inside each household overnight for 3 consecutive nights, 7 days after each round of MDA in year 1 (18 clusters) and 7 days after the 3rd round of MDA in year 2 (24 clusters). There will be three further nights of trapping during the peak transmission survey. *An. gambiae* s.l. will be identified morphologically.^54^ Parity, estimating mosquito survival, will be done using the Detinova ovarian tracheation method.^55^These mosquitoes will also be used to estimate cluster-level and trial arm-level species composition (proportion of species present within *An. gambiae* complex), population density (number of mosquitoes/trap/night and a proxy for human biting rate) and sporozoite detection using CSP ELISA.^56^ The entomological inoculation rate (EIR), a proxy for human exposure to infectious mosquitoes and a key indicator of local transmission, will be estimated using these data.^57^Anopheline mosquitoes will be reared from locally caught larvae during the year 2 rainy season. Batches of 100 adult females will be tested for resistance to alpha-cypermethrin, permethrin and deltamethrin, with and without the synergist piperonyl butoxide, using CDC bottle bioassays and WHO test tubes at once, two and five times the discriminating dose.^58 59^ Two hundred mosquitoes, including all resistant individuals, will undergo PCR species identification.^60^DBS samples positive for *P. falciparum* DNA will undergo further extraction, amplification by PCR^61^ and sequencing using Illumina-based technology to identify genetic mutations previously associated with antimalarial drug resistance, including polymorphisms in *pfkelch, pfmdr1, pfcrt* and *pfexo* genes, before being analysed using bioinformatic tools.^62 63^ Selective whole genome amplification steps will be conducted on the initial DNA extract to increase the quantity of *P. falciparum* DNA. A cohort of RDT-positive malaria patients will also be recruited from select health centres during the rainy season to provide serial DBS throughout treatment. These will then undergo qPCR analysis for evidence of treatment success/failure and identification of resistance markers as described above.AE data will be collected actively by distributors during MDA and for 48 hours after, and passively by sensitising participants and health centre nurses to report AEs. ASCs will monitor births, deaths and miscarriages. Supervisors will send daily reports to the trial manager, who will generate annual reports for the Data Safety Monitoring Board (DSMB). Cross-sectional and cohort surveys include post hoc questions on AEs. All doses will be directly observed. *Loa loa* is not endemic to this region, greatly reducing the risk of IVM-associated encephalitis. Appropriate health-seeking advice will provided by distributors to all participants reporting AEs.A population-based cross-sectional survey will be performed in all clusters during the 2023 dry season, that is, after all MDA has been delivered: 100 households will be randomly selected from household-head lists in each cluster yolk, and 1 child aged 2–10 years invited to participate from each household. Multiple children will be invited if the sample size is not met. Skin will be systematically examined to identify scabies, and impetigo in positive cases. Headlice examination and fine-tooth combing above a white cloth will occur over 10 min. Bedframes, mattresses, nets and adjacent walls will be inspected with torchlight for signs of bedbugs, or eggs, over 10 min. A stool sample (5 g) will be collected and stored in ethanol to undergo multiplex parasite PCR (STH, Strongyloides).^64–66^ DBS will be collected for serological testing for LF, strongyloidiasis and STH.^67–69^MDA distributors enter administration data into forms listing every householder, including absent members, and capture data on daily refusals, absences and exclusions. These forms generate a de facto census and can be used calculate monthly cluster-level coverage, absence, refusal and exclusion statistics.Qualitative and quantitative analysis of MDA acceptability, feasibility and access, including population movement, will be outlined in a separate protocol.Cost-effectiveness analysis will be detailed in a separate protocol.

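### The serology half of secondary outcome 4 is named as incidence in the child cohort but is analysed only by outcome 5's MFI, seroprevalence and age-derived seroconversion methods, which do not use the serial samples within a child

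*Protocol article*

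**What the plan says.** The list of secondary outcomes defines outcome 4 as "Incidence of malaria infection identified by qPCR and serological analysis during the same period in this cohort of children". The period is the one named in outcome 3: the intervention and the peak transmission season. Outcome 5 is listed separately and is a prevalence: "Age-adjusted prevalence of serological markers indicating recent exposure to" *P. falciparum*.

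Under Assessment of outcomes, Secondary, the cohort is described: "Cohorts of 50 children aged 5–14 years will be followed in 18 clusters". Visits fall 7–14 days after each MDA round, "as well as during the peak transmission surveys for a total of 8 timepoints". Because "A new cohort will be selected in year 2", each child has about four visits in one season. On sampling the text says "A DBS will be taken for molecular and serological analysis". The assessment of outcome 4 itself is one line: "Assessed as for outcomes 3 and 5".

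The Data analysis plan, Secondary outcomes, analyses the qPCR half of outcome 4 like outcome 3, with cluster-level incidence rates. For serology it has one sentence: "Serological analysis described in outcome 5". Outcome 5 there contains three comparisons: MFI by mixed linear regression with a random effect for cluster, seropositivity compared like the primary outcome, and cluster-level seroconversion rates from serocatalytic models fitted to seroprevalence by age and compared by t-test.

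**The concern.** The endpoint and its analysis measure different things. Incidence over a season needs an event, children at risk of it, and time at risk. The article states none of these for serology, and the method it refers to supplies none.

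- **Seropositivity prevalence** counts a child who converted years ago the same as one who converted this season.
- **MFI with only a cluster random effect** compares levels. It does not look at change within a child.
- **The seroconversion rate** comes closest. Derived from seroprevalence by age, it averages the force of infection over the child's life, and most of a 5–14-year age curve was laid down before the trial.

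The design could measure the named endpoint, because the same child is bled repeatedly within a season and conversion can be seen directly. As written, a weak or null contrast on outcome 5's measures could be reported as no effect of ivermectin on serological incidence when the measure was insensitive to one season's change.

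**Working it through.** **1. The plan's own figure.** The only power statement is for the primary outcome: above 80% with 12 clusters per arm, 200 per cluster, 10% against 5%, coefficient of variation 0.46. With c = 1 + (z₀.₉₇₅ + z₀.₈)² [p₀(1−p₀)/m + p₁(1−p₁)/m + k²(p₀² + p₁²)]/(p₀ − p₁)², the bracket is 0.00045 + 0.0002375 + 0.2116 × 0.0125 = 0.0033325. So c = 1 + 7.849 × 0.0033325/0.0025 = 11.46, and 12 per arm gives about 82%. The figure reproduces. It does not bear on outcome 4, for which no power is claimed.

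**2. Endpoint against analysis.**

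| Outcome | Named as | Stated analysis | Uses change within a child? |
|---|---|---|---|
| 4, qPCR | incidence | cluster incidence rates, t-test | incidence-based |
| 4, serology | incidence | as outcome 5 | no |
| 5 | age-adjusted prevalence | MFI, seroprevalence, age-derived rate | no |

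**3. Dilution (illustration).** The document gives neither the half-life of seropositivity nor a pre-trial seroconversion rate. Assumed: half-life 0.5–20 years (reversion ρ = ln 2/half-life); pre-trial rate λ of 0.05, 0.1 or 0.3 per year; ages 5–14; one season of T = 1/3 year carrying the year's exposure. That exposure is at f = 50% of its pre-trial level in control and 25% with ivermectin, a true halving.

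- Entry prevalence at age a: λ/(λ+ρ) × [1 − exp(−(λ+ρ)a)]
- Season rate: λₛ = λf/T
- End prevalence: λₛ/(λₛ+ρ) + [entry − λₛ/(λₛ+ρ)] × exp(−(λₛ+ρ)T)
- New seroconversion among seronegatives: 1 − exp(−λₛT)

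Example, λ = 0.1: λₛ is 0.15 and 0.075, and new seroconversion is 0.049 and 0.025, ratio 0.51. With a half-life of 0.5 years (ρ = 1.386), mean prevalence goes from 0.067 at entry to 0.079 and 0.061, ratio 0.77. With 5 years (ρ = 0.139) it goes from 0.371 to 0.384 and 0.369, ratio 0.96.

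Ranges over the three values of λ (reversion fixed at its true value when fitting the rate):

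| Half-life | New seroconversion ratio | Prevalence ratio | Age-derived rate ratio |
|---|---|---|---|
| 0.5 y | 0.50–0.52 | 0.77–0.78 | 0.73–0.76 |
| 1 y | 0.50–0.52 | 0.86–0.87 | 0.81–0.85 |
| 5 y | 0.50–0.52 | 0.96–0.97 | 0.91–0.95 |
| 20 y | 0.50–0.52 | 0.98–0.99 | 0.95–0.97 |

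**4. Power (simulation, 20,000 trials per setting).** From the document: 50 children per cluster, 18 clusters (9 per arm assumed), and 0.46 borrowed from the primary outcome. Assumed: conversion of 20% of seronegatives in control and 10% with ivermectin; between-cluster SD of entry seroprevalence 5–10 points; no reversion; no misclassification; equal entry seroprevalence by arm, as could hold in year 1. The expected prevalence difference is (1 − entry seroprevalence) × 10 points, so 6 points at 40% entry.

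| Entry seroprevalence | Power, seroprevalence | Power, within-child conversion |
|---|---|---|
| 20% | 26–37% | 60% |
| 40% | 17–25% | 54–55% |
| 60% | 11–16% | 45–46% |

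**5. Where the power gain shrinks.** At 40% entry:

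- If 30–50% of entry positives revert during the season, seroprevalence power is 23–32%. It is 27–43% if a new infection keeps such a child positive.
- With 5–10% false conversions among seronegatives, within-child power falls to 42–48%.
- If ivermectin clusters enter year 2 six points lower, seroprevalence power is 48–69% against about 55%. At 60% entry it is 38–60% against 45–47%.

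**The case against.** The strongest reply is that outcome 5 does contain an incidence-type measure, the seroconversion rate, compared between arms by t-test. That is correct, and a reader who infers that nothing in the serological plan resembles incidence goes too far. What stands is narrower: this rate comes from seroprevalence by age, so it is not incidence during the follow-up season, and in the illustration it is diluted almost as much as prevalence.

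A reader might also infer that new infections are swamped by old antibody. The document does not support that as a general statement. It gives no half-lives and no entry seroprevalence, outcome 5 targets recent exposure, and the panel mixes markers of recent and long-term exposure. For short-lived markers about half the effect remains; near-loss applies to markers lasting years.

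A third tempting inference is that within-child analysis is more powerful throughout. The simulation omits the MFI and seroconversion-rate comparisons, and its assumptions favour the within-child analysis. In year 2 a new cohort enters after a year of MDA, the arms may already differ, and the advantage can vanish or reverse.

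Finally, an article condenses its source, and event definitions often sit in a SAP. But the article does not leave the method open. It assigns one, in both the assessment and analysis sections, and that method does not estimate the named endpoint. The reference to outcome 3 in the assessment section supplies incidence for qPCR; the analysis section carries this through for qPCR only.

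**Conclusion.** The point holds in a limited form. The serology half of outcome 4 is named as seasonal incidence, and the stated analysis does not estimate it in either year. The qPCR half is unaffected, so the cohort still yields an infection incidence. The matter concerns half of one of 15 secondary outcomes.

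The size is assumption-based: dilution is partial for short-lived markers and almost complete for those lasting years. The power advantage of a within-child analysis (about 55% against 17–25% at an assumed 40% entry seroprevalence) belongs to year 1, rests on no reversion and no misclassification, and should not be claimed for year 2. Even then power is modest.

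**What to change.** For outcome 4, replace the cross-reference with a within-child definition:

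- **Event:** seronegative at one cohort visit and seropositive at a later visit in the same year, for recent-exposure antigens named before unblinding. A preset rise in MFI, above assay variation, serves as a supportive definition.
- **Rate:** events per child-time at risk in each cluster, compared between arms as for outcome 3.
- **Years:** report years 1 and 2 separately.
- **Supporting results:** keep outcome 5's prevalence, MFI and seroconversion rate. Add a child-level random effect wherever repeated MFI is modelled.

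The cost is analysis text and programming; the blood spots and assays are already planned. The Trial status section places laboratory testing ahead of statistical analysis, so the definition can be set while the analysts are blinded.

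The downsides should be stated with the result. Children seropositive at entry leave the main count. The earliest cohort sample follows MDA round 1, so there is no pre-intervention cohort baseline. In year 2 the seronegative set may already differ by arm, so that result is conditional on entry status and leaves out the effect accumulated in year 1.

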### Study design

This is a quadruple-blind (participant, intervention provider, investigator and analyst) cluster-randomised placebo-controlled trial.

Twenty-four clusters have been assigned in a 1:1 ratio to one of two trial arms using restricted randomisation^44^:

Intervention (DP and IVM MDA).Control (DP and IVM-placebo MDA).

Restriction variables included population, baseline *P. falciparum* prevalence (qPCR and RDT), vector density, SMC coverage and presence of a health centre. Of 100 000 randomisations, the final randomisation was selected from the approximately 10% satisfying the criteria.

This protocol was developed using SPIRIT reporting guidelines.^45 46^ A timeline is shown in figure 1.

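### Species proportions (secondary outcome 8) are to be compared between arms by a χ² test with no cluster term, although clusters were randomised: wrong as written, moderate severity

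*Protocol article*

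**What the plan says.** Under Study design, the unit of allocation is the cluster: "Twenty-four clusters have been assigned in a 1:1 ratio to one of two trial arms using restricted randomisation". Under Assessment of outcomes, Secondary, the light-trap mosquitoes of a cluster all come from a single place: "One yolk village will be randomly selected per cluster". The same mosquitoes supply species composition, density and sporozoite rate.

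Under Data analysis plan, Secondary outcomes, the sentence for outcome 8 reads: "The proportion of each species identified, and mosquito densities, will be presented by cluster and arm, and compared using χ^2^ and t-tests". It continues with "Adjustment will be made for study month and year" and "Differences, 95% CIs and p values will be presented". The comparison is therefore inferential and not only descriptive.

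The neighbouring entomological outcomes are handled differently in the same section:
- Parity: "Cluster-level anopheline parity will be compared between arms using a t-test".
- Sporozoite rate (SR): "SR will be compared between arms using a t-test on cluster-level SR".
- Entomological inoculation rate (EIR): "EIR will be compared with a t-test on cluster level summaries".

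**The concern.** Taken in order, the sentence for outcome 8 pairs χ² with the species proportions and the t-test with the densities. An ordinary χ² test of species by arm is computed from pooled counts, so each mosquito contributes as an independent unit. The arms differ by allocation of clusters, not of mosquitoes, and mosquitoes trapped in the same village share local breeding sites. If that makes species mix more alike within a cluster than between clusters, the variance used by the test is too small.

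The consequence would be a p value that is too low, and any CI computed from mosquito counts would be too narrow. A spurious difference in species mix would also affect how the other mosquito results are read, because species is an adjustment variable for parity and SR.

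**Working it through.** **1. The plan's own figure.** The article states no power or error rate for the species comparison. Its one power statement, under Assessment of outcomes, Primary, is more than 80% with 12 clusters per arm, 200 people per cluster, 10% versus 5% and a coefficient of variation of 0.46. The Hayes–Bennett formula, with two-sided 5% assumed, gives:

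- Variance term = 0.10×0.90/200 + 0.05×0.95/200 + 0.46²×(0.10² + 0.05²) = 0.00045 + 0.00024 + 0.00265 = 0.00333.
- Clusters needed per arm = 1 + (1.96 + 0.8416)² × 0.00333/0.05² = 11.46, so 12.
- Power with 12 per arm = Φ(√(11 × 0.0025/0.00333) − 1.96) = 81.9%; a noncentral t check gives 81.8%.

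The figure reproduces. The primary design allows for clustering, so the species comparison departs from the plan's own practice.

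**2. Inputs for the species test.** From the article: 24 clusters allocated 1:1, so 12 per arm; one village per cluster; a χ² test; 95% CIs, from which a two-sided 5% level is assumed. Not in the article, and therefore assumed: the number of mosquitoes per cluster identified to species (n) and the species ICC.

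**3. Formula.** With equal catches the design effect is DE = 1 + (n − 1) × ICC. The true size of an unadjusted χ² test at nominal 5% is 2 × [1 − Φ(1.96/√DE)]. A CI from the same counts is too narrow by a factor of √DE.

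| n per cluster | ICC | DE | True size | √DE |
|---|---|---|---|---|
| 20 | 0.01 | 1.19 | 7% | 1.09 |
| 20 | 0.05 | 1.95 | 16% | 1.40 |
| 50 | 0.01 | 1.49 | 11% | 1.22 |
| 50 | 0.05 | 3.45 | 29% | 1.86 |
| 100 | 0.01 | 1.99 | 17% | 1.41 |
| 100 | 0.05 | 5.95 | 42% | 2.44 |
| 100 | 0.10 | 10.9 | 55% | 3.30 |

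Example: n = 100, ICC = 0.05. DE = 1 + 99 × 0.05 = 5.95; 1.96/2.44 = 0.80; 2 × [1 − Φ(0.80)] = 0.42.

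**4. Where the trial might lie.** The trapping plan gives 10 households × 3 nights × 4 occasions = 120 trap-nights per trapped cluster in year 1, and 15 × 3 × 2 = 90 in year 2. If one mosquito per trap-night were identified to species (an assumption), n would be about 90. The true size would then be about 10% at ICC 0.005, 15% at 0.01, 40% at 0.05 and 53% at 0.10.

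**5. Simulation check.** Beta-binomial data were generated with 12 clusters per arm, no arm effect, a mean species proportion of 0.8 or 0.9 (assumed), ICC 0.02 to 0.20 and 20,000 replicates per setting. At a proportion of 0.8 and ICC 0.05, the χ² test rejected in 15.7%, 29.3% and 41.9% of replicates for n = 20, 50 and 100, in line with the table. With unequal catches (coefficient of variation 0.7, assumed) the figures rose to 20.2%, 35.4% and 48.7%. A t-test on cluster-level proportions rejected in 4.1% to 5.0% across all settings.

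**6. Number of clusters.** The simulation uses 24 clusters. Post-MDA trapping in year 1 covers only 18. The formula in step 3 does not contain the number of clusters, so the size of the χ² test is not changed by this. The cluster-level t-test would have 16 degrees of freedom in place of 22.

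**The case against.** The article never says that mosquitoes are treated as independent. It names no unit for this comparison, does not call the χ² test unadjusted, and does not say that the two tests apply respectively. It also promises adjustment for month and year, differences and CIs, none of which a plain contingency-table test delivers, so some further model may be intended. The authors handle clustering in the primary outcome, parity, SR, EIR and the antibody-intensity model, which suggests compressed wording as much as a deliberate mosquito-level analysis. The fuller protocol or the SAP may settle it.

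Part of this stands. The mosquito-level unit is the natural reading, not an explicit statement. The point survives because the article names a test, and that test, taken as named, does not respect the randomised unit. This is a stated choice and not a detail left out. The phrase about cluster and arm describes how results are presented and does not turn a χ² test into a cluster-level one. Month and year adjustment does not replace a cluster term, nor do the age, bed net and health centre adjustments promised generally under Primary outcome.

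A reader might also infer that the inflation is certainly severe, or that the trial will often report a false species shift. The documents do not support that. They give no species ICC, no catch per cluster and no data on how species mix varies between islands; they say only that one species predominates at peak transmission.

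**Conclusion.** Wrong as written, of moderate severity. With χ² as the named test and no cluster term, the species comparison is anti-conservative whenever species mix is correlated within clusters, which is plausible with one village per cluster on largely separate islands. Its direction follows from the design; its size does not. Under the assumed values the true size of the nominal 5% test runs from about 7% (20 per cluster, ICC 0.01) to about 42% (100 per cluster, ICC 0.05) and 55% (100 per cluster, ICC 0.10). It is mild only if catch and ICC are both small. The narrowing of the CI by √DE applies if the interval is built on mosquito counts; the article does not say how it will be obtained.

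It would be tempting to read this as a threat to the trial's main conclusion. It is not: it concerns one component of one of 15 secondary outcomes. The primary analysis and the parity, SR and EIR comparisons are explicitly at cluster level, and no decision in the article depends on the species p value.

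**What to change.** Replace the χ² test by a t-test on cluster-level species proportions, reporting the difference, 95% CI and p value from that analysis. This matches the method for parity and SR. State the number of clusters: 18 for the year 1 post-MDA trapping and 24 for year 2. If several species categories are to be tested together, use a cluster-adjusted test, such as a Rao–Scott χ² or a model with a cluster random effect. Carry the month and year adjustment within the cluster-level or random-effect analysis.

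The cost is a change of wording. Cluster-level proportions are already to be tabulated, and no further samples or laboratory work are needed. Under Trial status, laboratory testing was still under way ahead of statistical analysis, so on that account the change could be made before the comparison is run.
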